## Abstract

**Background:**

While cesarean section is an essential life-saving strategy for women and newborns, its current overuse constitutes a global problem. The aim of this formative research is to collect information from hospitals, health professionals and women regarding the use of cesarean section in Argentina. This article describes the methodology of the study, the characteristics of the hospitals and the profile of the participants.

**Methods:**

This formative research is a mixed-method study that will be conducted in seven provinces of Argentina. The eligibility criteria for the hospitals are (a) use of the Perinatal Information System, (b) cesarean section rate higher than 27% in 2016, (c) ≥ 1000 deliveries per year. Quantitative and qualitative research techniques will be used for data collection and analysis. The main inquiry points are the determining factors for the use of cesarean section, the potential interventions to optimize the use of cesarean section and, in the case of women, their preferred type of delivery.

**Discussion:**

It is expected that the findings will provide a situation diagnosis to help a context-sensitive implementation of the interventions recommended by the World Health Organization to optimize cesarean section use.

*Trial registration* IS002316

**Plain English Summary:**

Cesarean section is an essential medical tool for mothers and their children, but nowadays its overuse is a problem worldwide. Our purpose is to get information from hospitals, health professionals and women about how cesarean section is used in Argentina. In this protocol we describe how we will carry out the study and the characteristics of the hospitals and participants. We will implement this study in seven provinces of Argentina, in hospitals that have more than 1,000 births each year, had a cesarean section rate higher than 27% in 2016 and use the Perinatal Information System. We will gather information using forms, surveys and interviews. We want to identify the factors that decide the use of a cesarean section, the potential interventions that can improve the use of cesarean section and, in the case of women, the type of delivery they prefer. We expect that this study will give us a diagnosis of how cesarean section is used in Argentina, and that this will help to apply the interventions that the World Health Organization recommends to optimize the use of cesarean section in our specific context.

## Background

During the past century, childbirth went from being a domestic, familiar and community matter to a professional medical act. Changes in how child delivery is perceived and in the use of interventions and new technologies resulted in significant health improvements and, at the same time, took the experience of childbirth out of the family setting and into hospital facilities [1]. One of the interventions that resulted from the improvements introduced by the change in the child delivery care model was cesarean section. Since then, it has become a fundamental life-saving strategy for women and newborns, and it is also one of the emergency OB strategies that the World Health Organization (WHO) considers essential [2].

Cesarean section is a surgery that is used to solve or prevent certain complications that occur during pregnancy or childbirth and to reduce health risks for women and newborns. However, like any surgical procedure, cesarean section presents some risks and its use implies greater costs for health systems [3–5]. The inappropriate use of this intervention is a cause of concern given the fact that, as in highly vulnerable social contexts some women do not have access to a cesarean section and in others it is unnecessarily used, it increases inequalities in the access to and use of health interventions in the population.

Though cesarean section rates higher than 15–20% have not shown to have a positive impact on perinatal results [6, 7], the sustained increase in cesarean section rates above those values is a global issue [7]. It is estimated that there was a 3.7% increase in the global average rate of cesarean section use during 2000–2015 and several countries have reported 40–50% cesarean section rates in their populations [7]. Despite the fact that cesarean section has specific clinical indications, there is usually no homogeneous criteria in the use of this intervention and the previously mentioned increase would be the result of a greater use of cesarean section without any clinical indication, mainly in high and middle income countries [6]. Financial incentives, availability of resources in the institutions, health services beliefs and skills, organizational culture aspects, women's characteristics and preferences, among other factors, affect OB practice and may determine the use of cesarean section [8–12].

Evidence has shown that when isolated interventions are used to address the situations and processes that lead to an increase in the use of cesarean section in clinical practice, the results obtained as to a reduction in its use are less effective [13]. Furthermore, multiple component interventions that include all the stakeholders involved (women, health workers and health systems) have shown to present a higher probability of reducing the incidence of unnecessary cesarean sections [13–15]. However, the implementation of this kind of interventions is very challenging given the diversity in health care organization, health services practices, the many barriers that must be overcome in order to introduce and sustain the changes promoted by these interventions and also because these interventions demand a change in individual behaviors and affect the organizational culture of services and institutions [13, 16]. This is why the WHO recommends that, before implementing any intervention, a formative research be carried out to identify and define why there is an increase in rates in a specific environment, why this is locally relevant, which the determining factors are for this phenomenon and what women and health professionals think within the framework of certain cultural rules pertaining to the specific contexts [13].

Both South America and the Caribbean are regions with some of the highest cesarean section rates in the world, and both show a sharp acceleration in their increase [7]. Argentina is no stranger to this situation: the national average rate in public health subsector institutions increased by 23% between 2010 and 2017, to reach 34.7% ranging between 28.4% and 57.7% in 2017 [17]. This heterogeneous increase would indicate that the use of cesarean section might be affected by reasons that are not necessarily clinical. In addition, according to a previous research, women in Argentina prefer vaginal delivery [9],which demands a better understanding of the role of women’s preferences as well as the dynamics of the decision-making process in maternal and infant health, and, more specifically, of the organizational cultures in which decisions as regards performing a cesarean section are made. It is also necessary to understand the relationship that health professionals and services have with women in the hospital obstetric care setting. In this context, formative research has great potential.

Formative research has shown to be key in the design, development and execution of health interventions as it makes it possible to identify the characteristics of the stakeholders involved and to adjust the interventions to the peculiarities of the socio-cultural and institutional contexts [18, 19]. This type of research informs about the stakeholders’ beliefs, values, attitudes, knowledge and behavior in relation to a particular problem and its context. Formative research also provides evidence as to why some interventions are effective and others are not, it makes it possible to understand which factors in the health care process contribute to making an intervention implementation satisfactory, and it identifies the culturally appropriate interventions to be tested [16].

The purpose of our formative research is to collect information from hospitals, health professionals and women as regards the conditions, use, preferences, and potential barriers and facilitators to inform the design and the implementation of non-clinical interventions aimed at optimizing the use of cesarean section in public maternity hospitals in Argentina. This article describes the design, research methodology, and profile of study samples and it is part of a series of publications.

## Methods

This study uses a mixed-method design that combines quantitative and qualitative data collection and analysis techniques. The quantitative techniques include an institutional form that collects the characteristics of the participating hospitals, an online structured survey questionnaire to be applied to the health services and an in-person interview to be applied to the women who gave birth at those hospitals. The qualitative aspect of the study includes a subgroup of hospitals and it is based on semi-structured interviews applied to key informants. Finally, after finishing the data collection stage, a working meeting will be held with the heads of services and heads of midwives in order to validate the preliminary results and explore some hypothesis that may facilitate the interpretation of findings.

Eligibility criteria for public hospitals across Argentina are the following: a) use of the national perinatal information system (SIP-gestión); b) cesarean section rate higher than 27% in 2016; c) more than 1000 deliveries per year [17].

Out of the 88 potentially eligible institutions, 24 were non-randomly selected from the six country regions. 19 institutions agreed to participate, out of which five were selected, one from each country region, except for the Patagonian region where the institution declined to participate and to apply the in-person interview to women and the semi-structured interview to key informants.

The project was approved by the Independent Ethics Committee of Centro Rosarino de Estudios Perinatales and by the provincial Ethics Committees and/or the Teaching and Research Committees at each of the selected hospitals pursuant to the requirements in each jurisdiction. It was also approved by two Ethics Committees of WHO, the Research Project Review Panel of the UNDP/UNFPA/UNICEF/WHO/World Bank Special Programme of Research, Development and Research Training in Human Reproduction (HRP) at the Department of Sexual and Reproductive Health and Research of WHO, and the WHO Research Ethics Review Committee, Geneva, Switzerland. In Argentina, the research protocol was registered in the RENIS database (number IS002316).

The data collection tools are designed to collect information regarding three dimensions: determining factors for the use of cesarean section, interventions that may optimize the use of cesarean section and, in the case of women, their preferences as to the type of delivery (vaginal vs. cesarean section) and the reasons for such preference. Four tools have been designed: (1) institutional form; (2) health professionals’ form to be completed online; (3) women's form to be completed during an in-person interview and (4) hospital key informants’ form to be completed during an in-person interview. Every tool, explained in detail below, will be tested before starting the fieldwork.

### Data collection and tools

The institutional form collects information regarding the structural and organizational culture aspects: type and characteristics of the institution (number of live births in 2017, number of cesarean sections, training for general practice and obstetric residents, availability of ORs, labor and delivery units, newborn intensive care and obstetric beds); production (number of deliveries and cesarean sections, human resources, availability of supplementary services, including motherhood comprehensive preparedness programs); availability of pain management interventions during labor; and conditions for accompaniment during labor and delivery. It is completed by an institutional focal point especially chosen for the research in coordination with the head of service.

The purpose of the health professionals’ online survey is to obtain their inputs and personal opinion about the three dimensions as well as about a set of institutional and clinical practices related to the use of cesarean section. This survey is sent to the whole eligible population, which includes all the (permanent staff and shift personnel) specialized physicians and obstetricians and residents at the obstetrics & gynecology and obstetrics services at the selected hospitals. The survey includes a participation consent (compulsory answer) and 41 questions, 36 of them with pre-established options and 5 open questions. The questions address the following variables: (a) role and healthcare work, including the number of deliveries/cesarean sections performed in a week, (b) cesarean section deliveries at the hospital, (c) agreement with certain determining factors for the use of cesarean section in relation to the institution, health professionals and pregnant women, (d) interventions to optimize the use of cesarean section at the hospital, and (e) use of monitoring cycles and improvement in quality of care. This tool has been designed with a five-option Likert scale with the options “strongly agree” and “strongly disagree” as extreme answering options. For the interventions, the questions address usefulness and feasibility. Up to four reminders will be sent for the survey, one every seven days until the four-week time frame of the field work is completed. To reinforce the survey confidentiality, the respondents’ gender will not be recorded.

The women's interview is applied to postpartum women eight hours after delivery. Inclusion criteria are the following: (a) having had one delivery (vaginal or cesarean section) at the participating hospital, (b) ≥ 15 years old, (c) the newborn had not required hospitalization in Neonatal Intensive Care Unit, and  (d) obtaining the informed consent. Based on the average number of childbirths per institution, a minimum total number of 450 completed interviews is estimated. For this purpose, the adopted strategy is the selection of a consecutive sample in which one woman out of four who has a vaginal or cesarean section delivery is taken every day of the week until the 3 months of the survey are completed or 130 cases in each hospital are included (whichever criteria is met first). This tool consists of a structured survey questionnaire with 18 closed questions and 9 open ones. The variables covered by the survey questions are the following: (a) reproductive history, (b) opinions and preferences as regards vaginal and cesarean section delivery, (c) labor and delivery process (including accompaniment), (d) reasons to perform a cesarean section, vaginal and cesarean section delivery advantages and disadvantages, and (e) women's preference in general. The survey is applied by a health care provider specially trained for this task (social worker, psychologist or nurse) who is not a member of the obstetrics and gynecology service to prevent any bias and to preserve confidentiality.

The interviews to key informants are applied to 25 health professionals (five per hospital). In order to guarantee an heterogeneity in responsibilities and roles in obstetrics care, heads of services, residents and physicians specialized in obstetrics & gynecology, midwives and midwifery residents will be interviewed. A 16 open questions guide is used to inquire about the following variables: (a) factors that affect the decision as to which type of delivery to provide; (b) reasons involved in the use of cesarean section (professional skills to handle a complex or dystocial delivery, delivery after a cesarean section, problems related to pain management, characteristics of the population to which they provide attention, legal aspects, etc.); (c) professional opinion regarding the use of cesarean section; (d) analysis of the obstetrics service indicators; (e) experiences with changes in such services; (f) professional predisposition to change; and (g) usefulness and feasibility of the interventions to optimize the use of cesarean section (ongoing training in obstetric emergencies, strategies to improve adherence to clinical guidelines and protocols, training in the performance of instrumental vaginal deliveries and management of other high risk situations using high fidelity simulations, application of Robson classification, organization of human resources, financial or other incentives, interventions aimed at women). Interviews are carried out by especially trained personnel external to the services, in-person or virtually at the convenience of the interviewed participants.

### Data analysis

For the quantitative analysis, the level of agreement with the statements will be described. The variance in the answers of health care professionals will be assessed to see whether they are more similar to the answers of other health professionals in the same hospital or to similar professions across different hospitals. For the women’s survey, data will be described as mean ± standard deviation (mean ± SD) or median (range) for continuous variables and percentages for categorical variables. Chi-square test will be used for categorical variables as group comparison. Preference for mode of delivery will be analyzed using univariate and multivariate analysis adjusting for maternal age, delivery mode on the index pregnancy, parity, history of miscarriage, and delivery hospital. Unadjusted Odds Ratio (OR) and adjusted OR and 95% Confidence Interval (CI) will be used. All statistical tests of hypotheses will be two sided and criterion for statistical significance will be set to α = 0.05. Statistical analyses will be carried out with Stata version 15.

Qualitative data will be thematically analyzed [20]. Also, as different actors interact in the processes under study, focus is placed on understanding, by means of detailed descriptions, the different points of view according to the role or experience throughout the process, captured in their own words, and in the specific contexts in which they take place [21].

Finally, a validation meeting will be held to present the results and facilitate their discussion by the research team members. This will be a whole working day in-person meeting.

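### The preference model omits previous cesarean, so the adjusted index-mode odds ratio is confounded if previous cesarean also affects preference

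*Protocol article*

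**What the plan says.** For the outcome of preferred delivery mode, the Data analysis section announces a univariate and a multivariate model. It fixes the covariates as follows: "adjusting for maternal age, delivery mode on the index pregnancy, parity, history of miscarriage, and delivery hospital". On the effect measure it says: "Unadjusted Odds Ratio (OR) and adjusted OR and 95% Confidence Interval (CI) will be used". The list names five variables and is not presented as provisional. It goes as far as history of miscarriage but does not name previous cesarean. No other part of the article adds previous cesarean to the model, stratifies by it or excludes women who have had one.

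Two places in Data collection and tools bear on this.
- For the women's interview, the obstetric entry criterion is "having had one delivery (vaginal or cesarean section) at the participating hospital", with no restriction on earlier births. The questionnaire's topics begin with "a) reproductive history, (b) opinions and preferences as regards vaginal and cesarean section delivery".
- In the key-informant guide, "delivery after a cesarean section" is listed among the reasons involved in the use of cesarean section.

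**The concern.** Neither of the two related covariates stands in for previous cesarean. Parity counts births without recording how they happened. Index mode describes only the current birth.

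A woman who has had a cesarean before is more likely to have one again, and that experience may shape what she prefers. If both links hold, women with an index cesarean differ from women with an index vaginal birth partly because more of them had an earlier cesarean. The index-mode OR then carries that difference as well as any association with the current birth.

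Preference and the reasons for it are one of the three dimensions the tools are built around, and the Discussion gives understanding preferences and their reasons as a purpose. The adjusted ORs are the effect estimates that Data analysis specifies for preference. A reader of the results will want to know whether preference follows the birth just experienced or an earlier one. The listed covariates cannot separate the two.

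**Working it through.** **What the article supplies.** It gives the covariate list, the effect measure, two-sided α = 0.05 and a minimum of 450 interviews. It gives no expected OR, no prevalence of previous cesarean and no association with preference. There is therefore no figure of the plan's own to reproduce for this point.

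**Who is in the sample.** The entry criterion speaks of one delivery at the hospital. It could be misread as first births only, but parity is a model covariate and reproductive history is asked, so parous women are included. Some of them will have had a cesarean.

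**Assumed inputs (none from the article).**
- 40% nulliparous before the index birth, 60% parous.
- 30% of parous women with a previous cesarean.
- Index cesarean in 35% of nulliparous women, 15% of parous women without a previous cesarean and 80% of those with one.
- True ORs for preferring cesarean: index cesarean 2, parity 1, previous cesarean varied from 1 to 3.
- Baseline preference for cesarean (index vaginal birth, no previous cesarean) varied from 5% to 20%.

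**Cells (share of all women).**
- Nulliparous: cesarean 0.40 × 0.35 = 0.140; vaginal 0.260.
- Parous, no previous cesarean: 0.42 × 0.15 = 0.063; vaginal 0.357.
- Parous, previous cesarean: 0.18 × 0.80 = 0.144; vaginal 0.036.
- Index cesarean overall: 0.140 + 0.063 + 0.144 = 34.7%. This equals the 2017 public-sector national average in the Background, but that is not a study-hospital figure and does not validate the other inputs.

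**Mechanism by hand (baseline 10%, previous-cesarean OR 3).** Among parous women, the share with a previous cesarean is 0.144/0.207 = 69.6% after an index cesarean and 0.036/0.393 = 9.2% after an index vaginal birth.
- Preference probabilities: vaginal, no previous, 0.100; vaginal, previous, odds 3/9, so 0.250; cesarean, no previous, odds 2/9, so 0.182; cesarean, previous, odds 6/9, so 0.400.
- Averaged over previous cesarean: vaginal 0.908 × 0.100 + 0.092 × 0.250 = 0.114; cesarean 0.304 × 0.182 + 0.696 × 0.400 = 0.334.
- The OR in parous women is (0.334/0.666)/(0.114/0.886) = 3.9. In nulliparous women it stays at 2.0. The model pools the two.

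**Full range.** Logistic regression was fitted to the expected cell values, with parity and index mode only. The ranges are over baselines of 5% to 20%.

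| Previous-cesarean OR | Index-mode OR, omitted (true 2.00) | Parity OR, omitted (1.00 with previous cesarean in the model) |
|---|---|---|
| 1 | 2.00 | 1.00 |
| 1.25 | 2.17–2.18 | 1.08–1.10 |
| 1.5 | 2.32–2.34 | 1.16–1.19 |
| 2 | 2.59–2.66 | 1.29–1.37 |
| 3 | 2.99–3.20 | 1.51–1.71 |

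With previous cesarean in the model, the index-mode OR returns to 2.00 in every row.

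**Other inputs.** Take 35% of parous women with a previous cesarean, index cesarean in 80% of them, baseline 8% and no true index-mode effect. The index-mode OR then becomes 1.18 to 1.89 for previous-cesarean ORs of 1.5 to 4. The direction is the same, and an association appears where none exists.

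**At 450 interviews (baseline 8%).** The model-based standard errors of the log index-mode OR without previous cesarean are 0.300, 0.293 and 0.282 for previous-cesarean ORs of 1.5, 2 and 3. The bias in standard-error units is ln(2.34/2)/0.300 = 0.52, ln(2.64/2)/0.293 = 0.95 and ln(3.15/2)/0.282 = 1.61. A nominal 95% interval then covers the true value about 92%, 84% and 64% of the time, from Φ(1.96 − d) − Φ(−1.96 − d), where d is the bias in standard-error units.

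**The case against.** Several objections have force.

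- **Parity.** A reader might infer that previous cesarean confounds both parity and index mode. It does not confound parity: a previous cesarean can only follow an earlier birth, so it lies on the pathway from parity to preference. The shift in the parity column above is a change of question (total versus direct association), not an error. This stands. What remains is that the parity OR averages two groups that may differ.
- **Link to preference.** The key-informant item supports a link to delivery mode, not to women's preference. Confounding needs both. This stands, and makes the claim conditional.
- **Magnitude.** Every input is assumed, and the illustration leaves out age, miscarriage and hospital. This stands, which is why a range is given.
- **Sampling error.** At 450 women, with a baseline of 8% and a previous-cesarean OR of 3, the fully adjusted OR of 2.0 has a 95% interval of about 1.05 to 3.83, which contains the biased 3.15. That is true, but bias does not shrink with more interviews, and coverage suffers even at 450.
- **Consequence.** A reader might infer that these ORs are the study's main inferential output and that the omission would misdirect the interventions. The article says neither. The study is formative, it asks for reasons directly with open questions, and it ties no intervention to the parity or index-mode OR.
- **Unseen documents.** Covariate coding may be set out in the full protocol. But the article states the covariate list itself, so the point criticises a stated choice and not a missing detail.

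**Conclusion.** The point holds for index mode, conditionally. The stated adjustment set omits a variable that precedes the index delivery and is linked to its mode. If previous cesarean also affects preference given the other covariates, the adjusted index-mode OR is confounded, and it is overstated when previous cesarean raises preference for cesarean. Under the assumed inputs, a true OR of 2 is reported as about 2.2 when the previous-cesarean OR is 1.25 and as 3.0 to 3.2 when it is 3. If that OR is 1, nothing changes. The article does not allow the actual size to be fixed.

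For parity the conclusion is narrower: the OR is not biased by the omission, but it hides any difference between parous women with and without a previous cesarean. Nor does the article show that previous cesarean goes unrecorded, since the reproductive-history questions may well capture it.

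**What to change.** Add previous cesarean to the preference model. A convenient form is a three-level obstetric history: no previous birth, previous birth(s) without cesarean, and at least one previous cesarean. This avoids the empty cell for previous cesarean in first births. If parity is coded as a count, keep birth number among parous women as well, so that replacing parity does not discard it. Confirm that the reproductive-history questions record previous cesarean, and report preference by the three groups.

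The cost is one sentence in Data analysis and about one extra degree of freedom. Under the assumed inputs 0.18 × 450 = 81 women would have a previous cesarean, enough to form a group. Because previous cesarean and index mode are correlated, the interval for index mode widens. In the illustration at baseline 8% and a previous-cesarean OR of 3, the standard error of the log OR goes from 0.282 to 0.331, a ratio of 0.331/0.282 = 1.17.
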